### Cost analysis

For the cost analysis, the mean treatment cost over the study period (from baseline till the end of the study) will be compared between the residents in the control and in the intervention group. Treatment costs will be compared using the independent samples *t* test for variables having a normal distribution or the Mann-Whitney *U* test for variables not having a normal distribution. These costs will be calculated in 2015 and 2016 values from the perspective of the health-care payer (NIHDI contribution plus patient co-payment, if applicable). Costs will include the costs of the intervention, the costs of medication and the costs of other health-care use (GP visits, consultations with specialised physicians, visits to emergency departments and hospitalisations). With respect to the latter, the duration of hospitalisations will be multiplied by the per diem hospitalisation prices to generate a proxy estimate of hospitalisation costs (this excludes hospital costs for medication, medical imaging and clinical biology, for which no data will be available) [32].

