### Allocation

Nursing homes were stratified by (a) province/region, (b) experience with multidisciplinary case conferences (as reported in the application file) and (c) type of medication delivery (by a hospital pharmacy or by one or more community pharmacies). Factors (b) and (c) were considered to be possibly significant covariates. Geographical location (factor a) was taken into account because the funding body (NIHDI), requested that (i) at least one NH from each province/region was given the opportunity to implement the intervention and (ii) the number of NHs allocated to each group was balanced per province/region.

In 4 of the 10 Belgian regions/provinces, only one NH applied. These 4 NHs were therefore immediately assigned to the intervention group. The characteristics of the other 59 NHs with regard to location (province/region), experience with case conferences and type of delivering pharmacy, were entered into Statistical Package for the Social Sciences (SPSS; version 22). This programme generated a series of blocks for each stratum and allocated NHs to control or intervention group randomly within each block. Allocation was performed by an independent researcher blinded to the identification of the NHs and not involved in the recruitment of NHs or residents. Thirty NHs were allocated to the intervention group (as stipulated by NIHDI) and 33 to the control group. Because of the nature of the intervention, it was not possible to blind NHs or HCPs to the intervention.

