### Data collection

Data will be collected at three points in time: at month 1 (baseline), month 8 and month 15 (end of study). Data collection is performed by the HCPs involved in the care of each resident through a web application. Administrative and clinical data (e.g. age, functional status) are collected by the nurse, comorbidities (past and current medical history) and laboratory values by the GP, and medication data by the pharmacist. In the middle (month 8) and at the end of the study (month 15), data on health-care use (hospital admissions, emergency visits, GP or specialist visits) will also be collected by the nurse and the GP.

Characteristics of NHs (e.g. number of beds, location) and administrative data about participating HCPs are collected at the beginning of the study (month 1) from the coordinating physician and respective HCPs. HCPs will be paid for data collection.

In the intervention group, HCPs are also requested to record data on each case conference (participants, time for preparation, duration, DRPs identified, interventions,…)

Access to the web application is secured and requires both the national electronic identity card and the entry on a list of registered HCPs. HCPs have only access to data collection files of NHRs for which they are responsible. Data export from the web application to the research database will be performed with the intervention of a trusted third party (TTP), who is responsible for data coding and small cell analysis. NHRs and HCPs will be known to the research team by study ID number only. The whole process was approved by the Privacy Commission (nb 14/095, 21/10/2014).

For qualitative data (see ‘Process evaluation’ section), all interviews and focus groups will be audio recorded and transcribed verbatim, and the transcripts will be pseudo-anonymised.

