### Data analysis

#### Quantitative analysis

Data from the trial will be analysed and reported in accordance with the CONSORT criteria. The baseline characteristics will be reported as mean (± standard deviation) or median (and P25; P75) values for continuous variables and as counts (percent) for categorical variables. Descriptive statistics will be used to evaluate differences between intervention and control group on baseline characteristics at the resident, physician and nursing home level. Continuous variables will be compared using Student *T* test or Wilcoxon rank-sum test for clustered data, as appropriate. Categorical variables will be compared using adjusted chi-square test for clustered data.

To assess the impact of the intervention on the primary outcomes, logistic regression will take into account the complex design issues of the study (clustering, stratification). A multivariable model will be built to adjust the analysis for potential confounders, i.e. the number of PIMs/PPOs at baseline per resident and other baseline characteristics of residents, GPs and NHs. The analysis will be conducted using the intent-to-treat analysis, i.e. all residents will be analysed as randomised. A per protocol analysis will also be performed as a secondary analysis.

The impact of the complex intervention on the secondary outcome measures will be assessed using descriptive data and in some cases, using appropriate statistical evaluation.

Data analysis will be performed using R software (Free Software Foundation, Inc., Boston, MA, USA). A *p* value <0.05 will be considered statistically significant.

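### Costs are to be compared with an unadjusted two-group test although month-1 medication data are available, so a systematic baseline cost difference would pass into the estimated effect and precision is lost

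*Protocol article*

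**What the plan says.** The Cost analysis section sets the target: "the mean treatment cost over the study period (from baseline till the end of the study) will be compared between the residents" of the two arms. It lists the components: "Costs will include the costs of the intervention, the costs of medication and the costs of other health-care use". It then fixes the method: "Treatment costs will be compared using the independent samples *t* test for variables having a normal distribution". The alternative, where normality fails, is given as follows: "or the Mann-Whitney *U* test for variables not having a normal distribution". No baseline covariate, stratification factor or cluster term is mentioned.

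Elsewhere the article supplies what an adjusted analysis would need:

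- **Data collection:** "Data will be collected at three points in time: at month 1 (baseline), month 8 and month 15 (end of study"). The people recording the data are named, including "comorbidities (past and current medical history) and laboratory values by the GP, and medication data by the pharmacist". Health-care use is listed for months 8 and 15 only.
- **Trial status:** baseline data were collected in April 2015, and the intervention was implemented from May 2015.
- **Allocation:** homes were stratified by province/region, case-conference experience (b) and type of medication delivery (c). "Factors (b) and (c) were considered to be possibly significant covariates".
- **Quantitative analysis**, for the primary outcomes: the logistic regression accounts for clustering and stratification, and "A multivariable model will be built to adjust the analysis for potential confounders, i.e. the number of PIMs/PPOs at baseline per resident", along with further features of residents, doctors and homes.

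**The concern.** The primary outcomes are protected against baseline differences, and cost, a named secondary objective, is not. The article gives no reason for treating them differently.

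Two features of the design make this matter:

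- The Recruitment section says that residents could not be included before group allocation. Homes and professionals were unblinded, so the residents enrolled may differ between arms.
- The Allocation section says that the only applicant home in each of four provinces went straight to the intervention arm.

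Either feature could produce a systematic difference in baseline medication cost. An unadjusted test would report part of it as a saving or an extra cost of the intervention. Even with no such difference, leaving out a predictive baseline value widens the interval around a result meant to inform policymakers.

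**Working it through.** **The plan's own figure.** There is none to reproduce. The Cost analysis section gives no effect size, standard deviation, correlation or power, and the Sample size section concerns the primary outcomes only.

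**Inputs from the article.** There are 30 intervention and 33 control homes (Allocation), and the average cluster size is 30 (Sample size), giving 30 × 30 = 900 and 33 × 30 = 990 residents. The four homes assigned without randomisation are 4/30 = 13.3% of the intervention arm.

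**Assumed inputs.** The correlation rho between month-1 medication cost and the cost outcome is taken as 0.3, 0.5 or 0.7. The cost ICC is taken as 0.05 or 0.10.

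**Step 1: precision.** Adjusting for the baseline value multiplies the variance by 1 − rho² and the interval width by √(1 − rho²). Power after adjustment is Φ((1.96 + z_power)/√(1 − rho²) − 1.96). For rho = 0.5 and 80% starting power: (1.960 + 0.842)/0.866 − 1.960 = 1.275, and Φ(1.275) = 89.9%.

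| Assumed rho | Variance factor | Interval width factor | 50% power becomes | 80% power becomes |
|---|---|---|---|---|
| 0.3 | 0.91 | 0.95 | 53.8% | 83.6% |
| 0.5 | 0.75 | 0.87 | 61.9% | 89.9% |
| 0.7 | 0.51 | 0.71 | 78.4% | 97.5% |

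**Step 2: a systematic baseline difference.** If the arms differ by d standard deviations in baseline cost, the unadjusted cost difference shifts by rho × d. For d = 0.2, chosen for illustration, the shift is 0.06, 0.10 and 0.14 SD at rho 0.3, 0.5 and 0.7.

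**Step 3: simulation.** The set-up was 63 homes of 30 residents, ICC 0.05, no true effect, and the same rho at home and resident level.

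- With d = 0.2, the mean unadjusted estimates were 0.062, 0.101 and 0.139 SD, and the mean adjusted estimates were about 0.
- With d = 0, the empirical standard error fell from 0.070 to 0.067 (rho 0.3), 0.072 to 0.063 (rho 0.5) and 0.073 to 0.053 (rho 0.7), in line with Step 1.

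**Step 4: chance imbalance, for scale.** Its standard error is √[(1 + 29 × ICC)(1/900 + 1/990)].

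- ICC 0.05: √(2.45 × 0.002121) = 0.072 SD.
- ICC 0.10: √(3.90 × 0.002121) = 0.091 SD.

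At rho = 0.5, about half of this (roughly 0.04 SD at ICC 0.05) passes into the cost difference. It is already part of the sampling error counted in Step 1. By comparison, the 0.10 SD shift in Step 2 is 0.10/0.072 = 1.4 standard errors of the unadjusted estimate.

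**The case against.** Several objections have force.

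- **An unadjusted difference is legitimate under random allocation, and chance imbalance is not a bias.** This stands. A cluster-correct unadjusted interval already covers chance imbalance, so it must not be counted as a second harm beside lost precision. The bias argument rests only on systematic differences from inclusion after allocation and from the four non-randomised homes.
- **The precision gain is not shown for total cost.** This stands. Total cost includes visits and hospital stays, which have no stated month-1 measure, so the relevant rho may be low. At 0.3 the gain is about 4 power points, and at 0.2 it is under 2.
- **Adjustment alone leaves clustering untreated.** This stands and shapes the fix. With 30 residents per home, ignoring clustering turns a nominal 5% error into about 8%, 21% or 32% at an assumed cost ICC of 0.01, 0.05 or 0.10, from 2[1 − Φ(1.96/√(1 + 29 × ICC))].
- **Separate terms for all ten provinces would backfire.** This also stands. The four single-home provinces would have no control home and would add essentially nothing, leaving in effect 26 against 33 homes. Ten provinces and two further factors, if binary, take 9 + 1 + 1 = 11 parameters with only 63 homes.
- **The article is condensed and allows suitable statistical evaluation of secondary outcomes.** This does not remove the point. The cost section names specific tests, so it is a stated choice and not a detail left to an analysis plan. Supporting adjusted analyses are not excluded, but none is stated for cost.

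A reader might also infer that delivery type is known to drive medication cost, or that the month-1 regimen is itself counted in the outcome. The documents state neither: they call delivery type only a possible covariate and do not say how medication cost is accumulated.

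**Conclusion.** The point holds. The cost comparison is fixed without adjustment although a pre-intervention medication measure is collected and the primary model uses baseline values and stratification. A systematic baseline difference would pass into the cost effect in proportion to rho, and explainable variance stays in the error term.

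The size rests on an assumed rho: variance falls by 9%, 25% or 51% at 0.3, 0.5 or 0.7, mainly for medication cost and less for total cost. The direction follows whenever baseline and follow-up cost are positively correlated. The near-zero adjusted bias in the simulation assumes that the imbalance acts only through baseline cost. Selection that month-1 medication cost does not capture would remain.

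It would go too far to conclude that the arms do differ at baseline or that the cost result will be biased. The article reports no baseline cost data; it shows only a design in which such a difference could arise. The point concerns a secondary outcome and does not touch the primary analyses.

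**What to change.** In the Cost analysis section, replace the two-group tests with a comparison of mean cost by regression that allows for clustering, through a random effect for nursing home, GEE or cluster-robust standard errors. The covariates should be:

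- arm;
- month-1 medication cost;
- case-conference experience;
- type of medication delivery.

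Report the adjusted mean difference with its interval for medication cost and for total cost, and keep the unadjusted difference as a descriptive row.

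Include province/region only in a form that keeps the four single-home provinces in the comparison, for example pooled into larger regions. Add a sensitivity analysis that excludes those four homes.

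The change needs no new data, residents or visits. It costs the pricing of the month-1 medication list and a slightly more complex model.

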## Methods/design

### Trial design

The COME-ON study is a multicentre, cluster, parallel-group controlled trial. Each NH represents one cluster. As the intervention is mainly provided at the level of HCPs, a cluster design was chosen to prevent contamination bias. The study design was developed in accordance with the Consolidated Standards of Reporting Trials (CONSORT) statement extension to cluster RCTs [27].

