### Recruitment

In order to have a sufficient (to improve generalisability) but reasonable (for convenience reasons) number of GPs involved, all participating GPs caring for at least three eligible residents were identified. If possible, a maximum of 12 GPs per NH was aimed for. The objective was to include 35 residents per NH. One member of the research team performed resident selection assisted by the head nurse, the coordinating physician or a representative of the management board. An algorithm was developed (available upon request) to support NHR recruitment. If there were more than 35 eligible residents, a random selection was made using a statistical software (Statistical Package for the Social Sciences (SPSS) version 22). Written informed consent was asked by physicians (GPs or coordinating physicians) or nurses to each resident or to a resident’s representative if the resident was not mentally competent (e.g. in case of severe dementia). Due to practical reasons, resident inclusion could not be performed before group allocation.

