### Sample size

Estimations of sample size calculations were performed for the two primary outcomes.First, we estimated that among residents who had at least one PIM/PPO at baseline, there would be a decrease of at least one of these PIM/PPO at the end of the study for 20 % of NHRs in the control group and 40 % in the intervention group. We considered a power of 80 % and a statistical significance of 5 %. To take into account, the cluster nature of the study, we inflated the standard sample size estimates by a factor, i.e. the design effect = 1 + *ρ*(*m* − 1), where *m* is the average cluster size and *ρ* is the estimated intracluster correlation coefficient (ICC) [31]. As Belgian data on the ICC for the primary outcome measure were not available, we made estimations for two extreme values, i.e. 0.05 and 0.5. In fact, based on what has been found in the other primary care research setting, the ICC can be reasonably estimated between 0.05 and 0.5. With an average cluster size of 30 NHRs and an estimated percentage of dropouts of 22 %, a total of number of 502 and 3175 NHRs will be required for ICC values of 0.05 and 0.5, respectively.Second, we estimated that among all residents, there would be at least one new PIM/PPO present at the end of the study as compared to baseline for 20 % of NHRs in the control group and 10 % in the intervention group. Similarly to the estimation for the first outcome, we considered two extreme values of ICC, i.e. 0.05 and 0.5. With an average cluster size of 30 NHRs and an estimated percentage of dropouts of 22 %, a total of number of 1223 and 7738 NHRs will be required.

As mentioned above, the funding body (NHIDI) determined a priori the number of NHs and NHRs for the COME-ON study. Based on the previous cluster studies, we can expect an ICC closer to 0.05 than 0.5; consequently, a total of approximately 1890 NHRs might be enough to detect a statistically significant difference.

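### The cost comparison names tests that ignore nursing-home clustering, and its rank-test fallback does not compare the mean cost that the plan sets out to compare (secondary analysis; should be fixed)

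*Protocol article*

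**What the plan says.** The Cost analysis section names its target: "the mean treatment cost over the study period (from baseline till the end of the study) will be compared between the residents" in the two arms. It then fixes the method: "Treatment costs will be compared using the independent samples *t* test for variables having a normal distribution or the Mann-Whitney *U* test", with the rank test reserved for non-normal costs. It mentions no adjustment for nursing home.

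The rest of the article treats the trial as clustered:

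- Trial design: "Each NH represents one cluster".
- Allocation: "Thirty NHs were allocated to the intervention group (as stipulated by NIHDI) and 33 to the control group".
- Sample size: the numbers are inflated by a design effect, 1 + ρ(m − 1).
- Quantitative analysis, baseline tables: "Categorical variables will be compared using adjusted chi-square test for clustered data", and the rank-sum test is also specified in its clustered-data form.
- Quantitative analysis, primary outcomes: the logistic regression is to account for clustering and stratification.

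**The concern.** There are two separate faults.

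**Clustering.** Residents of one home share a delivering pharmacy chosen by the home, overlapping GPs and, in the intervention arm, the cost of home-level meetings. Intervention cost is part of the total being compared. Some within-home correlation of cost is therefore plausible. If it is present, a test that counts every resident as an independent observation understates the standard error and rejects too often.

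**The quantity tested.** The target is a mean. Costs that include hospital stays are usually skewed, so the stated rule would normally lead to Mann-Whitney. That test compares rank distributions and yields no difference in means.

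The stake is the cost result, a declared secondary objective calculated from the perspective of the health-care payer, which also funds the study. A payer needs the mean difference and an honest statement of its uncertainty.

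**Working it through.** **Inputs from the protocol article.** 30 intervention and 33 control homes (Allocation). Recruitment target: "The objective was to include 35 residents per NH". Planning values: "With an average cluster size of 30 NHRs and an estimated percentage of dropouts of 22" per cent, and "We considered a power of 80 % and a statistical significance of 5" per cent (Sample size). ICC for the primary outcomes between 0.05 and 0.5, expected nearer 0.05. No cost ICC is given, so I assume 0 to 0.10.

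**Step 1. Reproduce the plan's own figures.** At ICC 0.05 and m = 30 the design effect (DE) is 1 + 0.05 × 29 = 2.45. I assume a two-sided 5% level and the arcsine formula. For 20% vs 40% this gives 80.3 residents per arm, so 2 × 80.3 × 2.45 / 0.78 ≈ 504 (stated: 502). For 20% vs 10% it gives 194.91 per arm, so 2 × 194.91 × 2.45 / 0.78 ≈ 1224 (stated: 1223). The figures reproduce to within rounding or a small difference of formula, so the plan does apply this design effect to its primary outcomes.

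**Step 2. True error of a test that ignores clustering.** The naive statistic has variance DE instead of 1, so the true two-sided error is 2 × [1 − Φ(1.96/√DE)].

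| Assumed cost ICC (m = 30) | DE | 1.96/√DE | True error |
|---|---|---|---|
| 0 | 1.00 | 1.96 | 5.0% |
| 0.01 | 1.29 | 1.73 | 8.4% |
| 0.02 | 1.58 | 1.56 | 11.9% |
| 0.05 | 2.45 | 1.25 | 21.0% |
| 0.10 | 3.90 | 0.99 | 32.1% |

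At ICC 0.05 the error is 17.8% if dropout cuts the cluster size to 30 × 0.78 = 23.4, and 23.3% at the recruitment target of 35. With m = 30, a correct interval is √2.45 = 1.57 times as wide as a naive one.

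**Step 3. Check by simulation.** 2000 runs, 30 vs 33 homes of 30 residents, no true difference, ICC 0.05.

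| Costs | Naive t test | Mann-Whitney | t test on home means |
|---|---|---|---|
| Normal | 20.2% | 19.4% | 5.2% |
| Lognormal (ICC set on log scale) | 15.8% | 21.0% | 5.0% |

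The 15.8% is lower largely because a log-scale ICC of 0.05 with total log variance 1 is (e^0.05 − 1)/(e − 1) ≈ 0.03 on the cost scale. The formula then gives DE = 1 + 0.03 × 29 = 1.87 and an error of about 15%.

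**Step 4. Does Mann-Whitney compare means?** No clustering, 900 vs 990 residents, 1000 runs.

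- Lognormal costs with equal means and log SD 0.8 vs 1.0: Mann-Whitney rejects in 99% of runs, the Welch t test in 4%.
- Equal medians, means 1.38 vs 1.65: Mann-Whitney rejects in 6%, Welch in 93%.

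**Step 5. Can the direction reverse?** Assumed inputs: routine cost averages 1, a hospitalised resident adds 5 on average, and the intervention adds 0.2 per resident.

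- Hospitalisation 26% vs 30%: the means are 1 + 0.2 + 0.26 × 5 = 2.5 and 1 + 0.30 × 5 = 2.5. Mann-Whitney declares the intervention costlier in 98% of runs; Welch rejects in 4.5%.
- Hospitalisation 24% vs 30%: the means are 2.4 and 2.5, so the intervention is cheaper. Mann-Whitney still declares it costlier in 92% of runs.

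The size depends on the assumed spread. Rerunning with lognormal costs, a log SD of 0.5 for routine and 0.8 for hospital cost gives these same percentages for Mann-Whitney; 0.8 for both gives about 88% and 73%. The mechanism is simple: a small added cost moves every intervention resident up the ranks, while a saving from fewer admissions falls on few residents and counts for little in ranks.

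**The case against.** The strongest defence is that an article condenses its plan, and that the Quantitative analysis section leaves room for suitable statistics on secondary outcomes and commits to CONSORT. That would answer silence. Here the article names the tests, and the specific sentence on costs governs the general ones. Nothing in the article extends the clustering adjustment to costs.

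Several limits do stand:

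- **Certainty.** A reader might infer that the cost p value is bound to be wrong. The article gives no cost ICC. The value 0.05 is its lower planning value for binary prescribing outcomes, borrowed here. At ICC 0 the t test would be valid.
- **One headline figure.** 21% belongs to one assumed ICC, m = 30 and a normal approximation. At ICC 0.05 the checks span about 16% to 23%.
- **Bias.** Ignoring clustering misstates the uncertainty of the mean difference; by itself it does not bias the estimate.
- **Early exit.** A reader might add that a whole-period cost total mishandles residents who die or leave. The article is silent on this, an analysis plan may cover it, and total cost with accrual ending at death is a legitimate payer quantity. It is not a fault in this text.
- **Intervals.** The article promises no confidence interval for cost, so none of its stated intervals is too narrow.

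**Conclusion.** The sentence is wrong as written, on two counts. First, both named tests assume independent residents in a trial that allocated nursing homes, so the p value is too small whenever the cost ICC is above 0. Under assumed ICCs of 0.01 to 0.10 with m = 30, the true error of a nominal 5% test runs from about 8% to 32%. Second, even at ICC 0, Mann-Whitney does not address the stated mean. It can reject when mean costs are equal, or point the opposite way to the mean difference; how often depends on assumed cost distributions that the article does not supply.

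This should be fixed, but it is confined to a secondary analysis. The documents do not support reading it as a threat to the primary outcomes, whose analysis accounts for clustering.

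**What to change.** Replace the sentence naming the two tests with text to this effect: the difference in arithmetic mean cost per resident between arms will be estimated whatever the skewness of the costs, using a method that takes the nursing home as the cluster, and reported with a cluster-adjusted 95% confidence interval and p value.

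A bootstrap that resamples whole nursing homes is sufficient. A mixed model or GEE with nursing home as the cluster and the stratification factors as covariates is an alternative. If a log link is used, the fitted ratio must be converted to a mean difference by marginal prediction. Drop Mann-Whitney as the test of mean cost.

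The change is to analysis wording only and needs no new data. The price is a wider interval and a larger p value than the naive tests would give: at an assumed ICC of 0.05 and m = 30, an interval about 1.57 times as wide.
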